#### Multifocal transcranial Current Stimulation (MtCS)

Multifocal transcranial Current Stimulation (MtCS) montage (F3 anodal; AF3, FC1, FC3, FC5, F5, return) will be used with the anode over the lDLPFC. This montage, guided by StarStim® computational modeling data (see Fig. 2), was planned with the intention of enhancing the activity of the lDLFPC. Active stimulation will consist of 2 mA MtCS for 20 min applied immediately before EMDR sessions. The same protocol and montage will be used for sham stimulation, but the protocol will be implemented by ramping down (slowly) the current immediately after the ramp up period, and by ramping up (slowly) the current right before the final ramp down portion of the session. This way, the subject will feel the ramp up and ramp down events, but will not receive a significant dose of stimulation. Thus, the patient will believe she is being stimulated normally, but there should not be any real effects, in order to control for placebo effects of the MtCS treatment. The device used will be the StarStim®, which is a wireless hybrid EEG/tCS 8-channel neurostimulator system. StarStim® is currently classified as an investigational device under US federal law.

**Fig. 2 Fig2:**
[figure not shown]
Multifocal transcranial Current Stimulation (MtCS) montage

In the case of patients who have been prescribed medication with effects on the nervous system, such as antidepressants, anxiolytic drugs, anticonvulsants or atypical antipsychotics, an individualized follow-up of the clinical outcomes will be carried out to ensure that there is no interaction with the brain stimulation [28]. Although the application of MtCS is painless, in the event that a participant, due to her medical condition, feels marked pain or very significant discomfort due to the application of the stimulation and asks to stop the stimulation, this decision will be respected and the participant will receive EMDR treatment only. Again, if other different adverse effects than those mentioned above occur, they will be reported to the PI, and, in the event they are considered to be related to MtCS, also to the Ethics Committee department and relevant regulatory bodies as required, indicating the expectedness, seriousness, severity, and causality of the adverse effect. However, as has been mentioned previously, no problems that are detrimental to the participant are anticipated, meaning no interim analyses or formal stopping rules have been planned.

During the time of the study, no participant may receive MtCS sessions in parallel.

#### Waitlist condition

The patients allocated to this condition will follow their usual treatment without receiving any other additional therapy. Treatment as usual consists of regular visits with the rheumatologist, psychiatrist, and general practitioners, who are responsible for prescribing and monitoring the pharmacological treatment, principally in form of analgesics such as non-steroidal anti-inflammatory drugs, opioids, paracetamol, and/or gabapentin, but also antidepressant drugs and anxiolytics/hypnotics. Health psychoeducation by the nursing service and therapeutic physical exercise are also included in the waitlist condition. The patients from the waitlist condition group will be offered 10 sessions of EMDR therapy when their participation in the research project has finished. This has been decided for ethical reasons, but also with the aim that participants in the waitlist condition complete the study and thus the dropout rate in this arm can be reduced.

### Outcomes

Demographic and clinical variables will be collected through a clinical interview using the medical history of the patients and a specific Case Report Form (CRF) designed for the study which will include age, educational level, personal and family history, drug use, current pharmacological treatment and previous psychological treatment. We will also use the MINI International Neuropsychiatric Interview [63], Spanish validation [64] to explore the principal psychiatric disorders from Axis I of DSM-IV and CIE-10.

Pain intensity will be assessed using the following scales:
Visual Analog Scale for pain (VAS pain) [65]: The VAS Pain consists of a straight horizontal line, usually 10 cm long, anchored between 2 verbal descriptors: “No pain” on the left side and “Unbearable pain” on the right. Scores are interpreted as follows: no pain (0–2), mild pain (2–4), moderate pain (4–6), severe pain (6–8), and maximum pain (8–10). This measure assesses the intensity of the perceived pain over the last 2 weeks.Pain Disability Index (PDI) [66], Spanish validation [67]. The PDI contains a list of 7 life categories that can be disrupted by chronic pain: family and home responsibilities, recreation, social activity, occupation, sexual behavior, self-care, and life-support activity. For each category there is a score from 0 to 10, higher scores mean greater disruption.Fibromyalgia Impact Questionnaire (FIQ) [68], Spanish validation [69]. The FIQ is a 10-item self-administered scale for measuring physical impairment due to FM over the last week. Higher scores indicate greater impact in functioning.

Psychological trauma and trauma-related symptoms will be evaluated using the following scales:
Global Evaluation of Post-traumatic Stress (EGEP-5) [70]. The EGEP-5 is a 55-item clinician-applied scale to determine current PTSD diagnosis, based on DSM-V criteria. There are three different sections: presence of traumatic events, symptoms, and functioning. The scale can determine a diagnosis of PTSD, specifying the presence of dissociative symptoms (depersonalization and derealization) and delayed expression.The Impact of Events Scale-Revised (IES-R) [71], Spanish validation [72]. The IES-R contains 22 items scored on a 5-point Likert scale, resulting in a score on 3 subscales (intrusion, avoidance and hyperarousal), with a total score ranging from 0 to 88. Higher scores represent greater distress. It measures the distress caused by a specific stressful life event over the previous 7 days.The Holmes-Rahe Life Stress Inventory [73], Spanish validation [74]. This scale lists 43 possible stressful life events, each with a respective score. Global scores under 150 indicate low levels of stress, scores between 150 and 299 indicate a 50% risk of stress-related disorders and scores above 300 represent an 80% risk of suffering from stress [73].The Childhood Trauma Questionnaire (CTQ) [75], Spanish validation [76]. The CTQ is a self-applied scale which includes a 28-item test that measure 5 types of childhood maltreatment: emotional, physical and sexual abuse, and emotional or physical neglect. A 5-point Likert scale (from 1 to 5) is used for the responses which range from “never true” to “very often true.” The final scores provide a severity score for each subscale from “none to minimal,” “low to moderate,” “moderate to severe,” and “severe to extreme.”Dissociative Experiences Scales (DES) [77], Spanish validation [78]. The DES consists of 28 questions about different experiences related to dissociation, excluding when the subject has been intoxicated. This test is scored by summing the percentage score given in answer to each question (from 0 to 100) and then dividing by 28. A total score higher than or equal to 30 corresponds with high levels of dissociation.Somatoform Dissociation Questionnaire 20 (SDQ-20) [79], Spanish validation [80]. The SDQ-20 is a 20-item self-report questionnaire measuring somatoform dissociation. Items refer to somatic symptoms and then ask if there is a known cause for them. The items are answered on a 5-point Likert scale and the symptoms with no known cause are summed to achieve the total score.

Anxiety and depression will be assessed using the following scale:
Hospital Anxiety and Depression Scale (HADS) [81], Spanish validation [82]. The HAD was created for detecting the presence of anxious and depressive disorders. It contains 14 items, 7 for each of the subscales (anxiety and depression), which can be rated from 0 to 3. A punctuation higher or equal to 11 indicates presence of affective disorder.

Quality of sleep will be assessed using the following scale:
Athens Insomnia Scale (AIS) [83], Spanish validation [84]. The AIS is a self-administered scale based on the ICD-10 criteria for insomnia. It measures sleep difficulties suffered over the previous three nights. It consists of 8 items evaluating sleep induction, awakenings during the night, final awakening, total sleep duration, sleep quality, wellbeing, functioning capacity, and sleepiness during the day. It is scored from 0 to 24 and higher scores mean greater difficulties.

Wellbeing will be assessed using the following scale:
Satisfaction With Life Scale (SWLS) [85], Spanish validation [86]. The SWLS is a 5-item self-administered scale measuring global cognitive judgment of satisfaction with one’s life. The items can be rated from 1 to 5, and lower scores indicate lower satisfaction.

All patients will be clinically evaluated at baseline/enrollment (*t*_1_), post-treatment (*t*_2_), and follow-up evaluation at 6 months from post-treatment (*t*_3_) (see Tables 1, 2, and 3). Personal participant data will be numerically coded and kept in a database in the Centre Forum Research Unit, who will be responsible for data maintenance and safety. Only the researchers involved in this trial will have access to this data. The database will contain the information of both the participants who finish the study as well as those who drop out, along with the corresponding causes for not completing the study. The Centre Forum Research Unit will be responsible for creating and maintaining the database.

**Table 1 Tab1:** Measurements to evaluate pain and FM impact

Clinical variable	Measurement interview/self-report	***t***_**1**_ Baseline	***t***_**2**_ Post-treatment 6 months	***t***_**3**_ Follow-up 12 months
Pain intensity	VAS pain	x	x	x
Pain disability	PDI	x	x	x
FM impact	FIQ	x	x	x

*VAS pain* Visual Analog Scale for pain, *PDI* Pain Disability Index, *FIQ* Fibromyalgia Impact Questionnaire

**Table 2 Tab2:** Measurements to evaluate psychological trauma symptoms

Clinical variable	Measurement interview/self-report	***t***_**1**_ Baseline	***t***_**2**_ Post-treatment 6 months	***t***_**3**_ Follow-up 12 months
Childhood trauma	CTQ	x		
PTSD	EGEP-5	x	x	x
Life events	The Holmes-Rahe Life Stress Inventory	x		
Trauma impact	IES-R	x	x	x
Distress associated to event	SUD	x	x	x
Dissociation	DES	x	x	x
Somatoform dissociation	SDQ-20	x	x	x

*CTQ* Childhood Trauma Questionnaire, *PTSD* Post-Traumatic Stress Disorder, *EGEP-5* Global Evaluation of Post-Traumatic Stress, *IES-R* Impact Event Scale-Revised, *SUD* Subjective Units of Distress, *DES* Dissociative Experiences Scale, *SDQ-20* Somatoform Dissociation Scale

**Table 3 Tab3:** Measurements to evaluate clinical symptoms, insomnia, and quality of life

Clinical variable	Measurement interview/self-report	***t***_**1**_ Baseline	***t***_**2**_ Post-treatment 6 months	***t***_**3**_ Follow-up 12 months
Comorbidity	MINI	x		
Anxiety	HADS-A	x	x	x
Depression	HADS-D	x	x	x
Insomnia	AIS	x	x	x
Quality of life	SWLS	x	x	x

*MINI* MINI International Neuropsychiatric Scale, *HADS-A* Hospital Anxiety and Depression Scale-Anxiety, *HADS-D* Hospital Anxiety and Depression Scale-Depression, *AIS* Athens Insomnia Scale, *SWLS* Satisfaction With Life Scale

### Sample size calculation

The main tests of the study will consist of assessing whether patients assigned to EMDR show different levels in the pain intensity variable using a standard formula for two-tailed *t*-tests. The total sample size required to detect large to very large effect size differences (Cohen’s *d* ≥ 1) between two groups with a significance level of 0.05 and statistical power of 80% is 13 and 26. Assuming 15% dropouts, we will aim to randomize 45 patients, i.e., 15 + 30, so that after removing ~ 15% dropouts we would have approximately 13 + 26.

### Data analysis

The distribution of the sociodemographic and clinical variables between groups at baseline will be summarized by descriptive statistics. We will use *t*-tests to compare pain levels at post-treatment and follow-up between groups (Waitlist vs EMDR; active-MtCS vs sham-MtCS). In order to avoid regression toward the mean and confusion effects, baseline levels of pain will be added as covariates, as well as age, depression and anxiety severity and number of years of education. Due to the sample size, no further analysis is expected. The statistical software used for the analysis will be R. For the principal statistical analysis, an intention to treat (ITT) analysis will be used, and multiple imputation for losses at follow-up. The dataset analyses during the current study will be available from the corresponding author on reasonable request.

## Discussion

This scientific paper presents the first protocol of a double-blind RCT to investigate whether EMDR is effective in the treatment of FM and its comorbid symptoms, and if its potential is boosted with the addition of MtCS. Patients with FM can be a great clinical challenge for healthcare professionals, due to their high comorbidities and unexplained symptoms [87, 88]. The etiology of FM is poorly understood [3], consequently leading to an erroneous interpretation of the disorder and its manifestations, resulting in a pattern of excessive and non-beneficial therapy [89]. Patients usually feel frustrated about their treatment options [90] and dissatisfied with the support received: 38% of FM patients in Spain state that the public health system is the entity which gives them the least support, despite 72% of the FM patients only visiting doctors within this system. This lack of satisfaction with current diagnostic and treatment options could explain why 87% of FM patients prioritize scientific research as the means to a painless future [91]. It is the duty of researchers and clinicians to study precipitators and susceptible populations to build beneficial therapy protocols [4], and thus it is imperative to recognize the evidence showing the importance of the psychological trauma as a trigger in the development, maintenance, and chronification of FM, and provide suitable therapeutic options to address this.

This protocol is innovative in combining the EMDR approach for treating psychological trauma and reducing pain levels with MtCS. This approach should also help treat comorbidity, which, according to the results of recently published works, may also improve FM symptoms [89, 92–94]. The stress-related antecedents of FM include early-life traumas, PTSD, depression, anxiety, and major life stress [95]. Therefore, since traumatic events can predispose individuals to FM, mood, and anxiety disorders and influence mental and physical health [91, 94], the interventions appearing in this protocol seem beneficial.

Although there are several studies showing high comorbidity between FM and PTSD [4], very few studies have been carried out testing interventions targeting trauma-related comorbidity, and those which exist are of low quality [4], due to factors such as a lack of control subjects, variability in PTSD and depression diagnoses, and the high associated comorbidity [6]. Thus, this study will be a useful addition to the extant literature, and it will shed light on the possibility of developing a larger RCT using a new psychotherapeutic approach for the treatment of FM.

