## Abstract

**Background:**

Fibromyalgia (FM) is a generalized, widespread chronic pain disorder affecting 2.7% of the general population. In recent years, different studies have observed a strong association between FM and psychological trauma. Therefore, a trauma-focused psychotherapy, such as eye movement desensitization and reprocessing (EMDR), combined with a non-invasive brain stimulation technique, such as multifocal transcranial current stimulation (MtCS), could be an innovative adjunctive treatment option. This double-blind randomized controlled trial (RCT) analyzes if EMDR therapy is effective in the reduction of pain symptoms in FM patients and if its potential is boosted with the addition of MtCS.

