**Methods:**

Forty-five patients with FM and a history of traumatic events will be randomly allocated to Waiting List, EMDR + active-MtCS, or EMDR + sham-MtCS. Therapists and patients will be kept blind to MtCS conditions, and raters will be kept blind to both EMDR and MtCS. All patients will be evaluated at baseline, post-treatment, and follow-up at 6 months after post-treatment. Evaluations will assess the following variables: sociodemographic data, pain, psychological trauma, sleep disturbance, anxiety and affective symptoms, and wellbeing.

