### Study design

Within a double-blind randomized controlled design, patients will be randomized to (1) Waitlist Condition, (2) EMDR + active-MtCS (20 sessions), or (3) EMDR + sham-MtCS (20 sessions). All subjects will continue to receive their treatment as usual (TAU), regardless of the group to which they have been assigned during the study. If a participant does not attend 3 sessions consecutively, she will be withdrawn from the study. Psychotherapists and patients will be kept blind for MtCS treatment conditions until the end of the trial, and raters will be kept blind to both EMDR and MtCS conditions. It is not possible for patients to be blind to the EMDR condition due to its use of bilateral stimulation. The experimental condition assigned to the participants will only be revealed if the patient abandons the study. Otherwise, the blind condition will be maintained until the end of the study. All patients will be clinically evaluated at baseline, at post-treatment, and at 6 months from post-treatment as follow-up.

Figure 1 shows a flow chart of the progress of the study.

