### Randomization

The main analysis will be the comparison between patients assigned to EMDR vs those not assigned to EMDR. The secondary analysis, only amongst patients assigned to EMDR, will be the comparison between patients assigned to active-MtCS vs patients assigned to sham-MtCS. Therefore, the individuals will not randomly be assigned to one of the three arms. Instead, the patients meeting the inclusion criteria will be randomized twice: first to EMDR vs non-EMDR, and then those in the EMDR group to active-MtCS or sham-MtCS. For the sake of brevity, only the randomization to EMDR vs non-EMDR is described here, because the randomization to active-MtCS vs. sham-MtCS is identical. The variables used for the randomization will be age, educational level, and pain intensity score. The first two patients will be randomly allocated to EMDR with *p* = 2/3. For each subsequent patient, the following biased coin algorithm will be applied: if a group includes at least two more patients than it would have to have to maintain the ratio 2 EMDR / 1 control, the patient will be randomly assigned to the other group with *p* = 0.6. Otherwise, there will be a simulation of the new patient as it was allocated to EMDR and calculate the between-group standardized difference in pain intensity variable, then simulate that the new patient is allocated to non-EMDR and recalculate the difference, and finally randomly allocate the patient to the group associated to the smallest difference with *p* = 0.6. This strategy decreases prognostic imbalances between groups because it decreases differences in potential co-founders, yet still includes randomization.

Once the randomization group has been obtained, the principal investigator (PI) of the study will inform the participants accordingly. If the participants have been assigned to the EMDR group, the coordinator will also contact the therapist responsible of the treatment.

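### The trial is called double-blind for the question whether EMDR reduces pain, but only the secondary comparison, active versus sham MtCS, is double-blind; in the main comparison unblinded patients rate their own pain

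*Protocol article*

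**What the plan says.** **The label.** The Abstract (Background) states: "This double-blind randomized controlled trial (RCT) analyzes if EMDR therapy is effective in the reduction of pain symptoms in FM patients". The Discussion says: "This scientific paper presents the first protocol of a double-blind RCT to investigate whether EMDR is effective in the treatment of FM". Both sentences go on to ask whether MtCS boosts the effect. Study design places all three arms, waitlist included, within a double-blind randomized design.

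**Who is blind to what.** The Abstract (Methods) states: "Therapists and patients will be kept blind to MtCS conditions, and raters will be kept blind to both EMDR and MtCS". Study design repeats this and adds: "It is not possible for patients to be blind to the EMDR condition due to its use of bilateral stimulation". Under Randomization, the principal investigator tells participants their group.

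**Which comparison is main.** Randomization states: "The main analysis will be the comparison between patients assigned to EMDR vs those not assigned to EMDR". The secondary analysis, within the EMDR patients only, "will be the comparison between patients assigned to active-MtCS vs patients assigned to sham-MtCS".

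**The endpoint.** Sample size calculation bases the main tests on pain intensity. Outcomes measures pain intensity with a VAS, a line between two verbal anchors, and says: "This measure assesses the intensity of the perceived pain over the last 2 weeks".

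**Limitations** covers drug treatment, the female-only sample, the small size and the scalability of MtCS. It does not mention self-reported pain in patients who know their group.

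**The concern.** For a pain VAS the patient is the assessor. In the main comparison she knows whether she is attending up to 20 hour-long sessions or waiting on usual treatment. Expectation, therapist contact and disappointment at being wait-listed can each move her rating, and all would favour EMDR. A rater who does not know her group only collects the score.

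What is at stake is how a positive main result may be described. Under the present wording it could be read as double-blind evidence that EMDR reduces fibromyalgia pain. The design supports a narrower statement: EMDR, given with active or sham stimulation sessions and added to usual care, compared with usual care alone, where expectation and contact cannot be separated from any specific effect of EMDR.

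**Working it through.** **Step 1. Set the two comparisons side by side.**

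| | Main: EMDR vs waitlist | Secondary: active vs sham MtCS |
|---|---|---|
| Patient | knows (Study design; informed under Randomization) | blind |
| Therapist | knows (delivers EMDR or does not) | blind |
| Rater | blind | blind |
| Source of the pain score | patient | patient |

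Double-blind describes the right-hand column. In the left-hand column the only blind party is the rater, who does not generate the endpoint. The text never uses the term self-rated for the VAS, but a mark for perceived pain can come only from the patient.

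**Step 2. See whether the design controls expectation in some other way.** The MtCS section includes a sham to deal with placebo response to stimulation. Nothing equivalent exists for EMDR, because under Waitlist condition the controls receive usual treatment only. The Background itself criticises earlier EMDR pain trials for lacking active comparators. The covariates in Data analysis (baseline pain, age, depression and anxiety severity, education) are baseline characteristics. They cannot remove a shift that arises because patients know their group after randomization.

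**Step 3. Reproduce the plan's own sample size.** Inputs from Sample size calculation and Randomization: d = 1, two-sided 0.05, power 80%, allocation 2:1. For a two-sample t-test, power follows from the noncentral t distribution with df = n1 + n2 − 2 and noncentrality d × √(n1·n2/(n1 + n2)).

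- 12 + 24: power 78.5%.
- 13 + 26: df = 37, noncentrality 1 × √(338/39) = 2.944, power 81.8%.

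So 13 + 26 is the smallest 2:1 size that reaches 80%, and the stated figure holds. With 15% dropout, 15 × 0.85 = 12.75 and 30 × 0.85 = 25.5, which agrees with the plan's approximate 13 + 26.

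**Step 4. Illustrate the effect of a bias.** Assume no specific effect of EMDR, and a shift of b SD in self-rated pain caused only by knowing the allocation. The documents give no value for b, so a range is shown. Noncentrality is b × 2.944 at 13 + 26.

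| Assumed b (SD) | Noncentrality | Two-sided rejection, 13 + 26 | Same, all 15 + 30 analysed |
|---|---|---|---|
| 0 | 0 | 5.0% | 5.0% |
| 0.2 | 0.589 | 8.8% | 9.5% |
| 0.3 | 0.883 | 13.8% | 15.3% |
| 0.4 | 1.178 | 20.9% | 23.5% |
| 0.5 | 1.472 | 30.0% | 34.0% |

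These are rates for an unadjusted t-test. Data analysis plans covariate adjustment, intention to treat and multiple imputation, so they are not the operating characteristics of the planned analysis.

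**The case against.** The strongest reply is that nothing is hidden. The Abstract sets out blinding by role, and Study design says outright that patients cannot be blind to EMDR. The sentences carrying the label also cover the MtCS question, which is blind for patients, therapists and raters, and the article's title concerns augmentation by MtCS. A waitlist on usual care is a legitimate comparator for a trial that calls itself exploratory and pragmatic and says its findings need replication in a larger sample.

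Most of this stands, and it lessens the fault. The waitlist is not the defect, and the title needs no change. But the disclosure does not reach the places where the claim is made. The Abstract's aim and the Discussion's opening still attach the label to EMDR efficacy without qualification, the Abstract's closing statement promises evidence on EMDR and pain without it, and Limitations omits the consequence. This is wording printed in the article, not a detail left to an analysis plan.

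A reader might go further and infer that the main comparison is simply open-label. The documents do not support that, because raters are blind to EMDR as well as to MtCS. A reader might also look to the clinician-applied EGEP-5 as a protected outcome. It still depends on the unblinded patient's answers, and it addresses PTSD, not pain.

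**Conclusion.** The point holds as a mismatch between label and design. Double-blinding covers the secondary comparison only. The main comparison is unblinded for patients and therapists, with blinded raters and a patient-reported endpoint that rater blinding does not protect. This rests on the protocol's own statements, plus the inference that a VAS of perceived pain is marked by the patient.

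The size of any bias is unknown. The figures of about 9% to 30% at 13 + 26 depend on the assumed shift of 0.2 to 0.5 SD and on an unadjusted completer t-test. A reader might take them as the trial's actual false-positive rate, but no figure in the documents supports that. The sample size reproduces and is not affected. The documents also give no ground to extend the criticism to the MtCS comparison, where the label fits.

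**What to change.** 1. In the Abstract (Background), Study design and Discussion, restrict double-blind to active versus sham MtCS. Describe EMDR versus waitlist as unblinded for patients and therapists, with blinded raters and a patient-reported endpoint.
2. In the Abstract (Discussion) and the main Discussion, limit the conclusion to EMDR (with active or sham MtCS sessions) added to usual care versus usual care alone, not separable from expectation and contact.
3. Add to Limitations that the main endpoint is rated by patients who know whether they receive EMDR.

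The cost is wording only: arms, sample size, outcomes and analysis stay as they are. The downside for the sponsor is a less favourable label for the main comparison.
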